#### Statistical analysis plan

2.8.3

The primary aim for comparisons of total hip aBMD at 12 months will be tested using a linear mixed model fit with total hip aBMD as the primary outcome and the following independent variables: visit (six and 12-months), treatment effect indicator (1 for risedronate; 0 for placebo), the treatment by visit interaction, participant sex (to account for randomization strata and sex as a relevant biologic variable), and baseline total hip aBMD value, assuming an unstructured covariance. The effect of the intervention at 12 months will be estimated using a contrast statement to test the 12-month treatment group difference using a 0.05 level of significance. Additional analyses will test the short-term effect by estimating the six-month treatment effect from the same model. Per protocol sensitivity analyses will be conducted similar to primary analyses, except using only the subset of patients who took at least five of the six prescribed pills (risedronate or placebo). The secondary aim outcome variables will be tested similarly as the first, separately modeling each outcome using six and 12-month outcomes as the dependent variables of the mixed linear model and all other covariates the same, except respective baseline values will be used in place of baseline total hip aBMD. Treatment effects at 12 months, the comparisons of primary interest, will be tested at a two-tailed α = 0.05 level using contrast statements. All models will use completers only, noting that mixed models with baseline covariate adjustments are fairly robust to missing data; [57,58] however, sensitivity analyses will be conducted to ensure results are not biased due to differential missing data. Tertiary aim treatment effects will use the same models as the first two aims changing only the outcome and baseline covariate and treatment effects will be tested at the α = 0.05 level. Additional analyses will explore whether changes in biomarkers mediate the relationship between risedronate and BMD. Our pilot data do not suggest that we will see clinically meaningful differences in treatment effects by race/ethnicity or sex. However, to explore the possibility of differential treatment effects, we will include sensitivity analyses using race/ethnicity or sex as an interaction variable with treatment assignment to determine whether treatment effects differ across race/ethnicity or sex. All analyses will be conducted using SAS v9.4 (Cary, NC) and R software.

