#### Data management and statistical approach

2.8.1

In accordance with best practices, data will be retained in a secure, password-protected electronic database. Dynamic reports and statistical analyses will monitor data quality. A participant-based inventory system will track recruitment, retention, adherence, and missing data from entry through exit, close-out, and final lock-down. Primary analyses will use intention-to-treat principles per CONSORT guidelines, with secondary analysis following a per protocol approach (including patients who are >80% compliant with the medication protocol) to assess whether protocol compliance affects observed intent-to-treat (ITT) results. Serious AEs will be reported within 48 h to maintain up to-date safety information for reporting to the Data and Safety Monitoring Board. All data will undergo range checks at the time of data entry and will be examined monthly by histograms and bivariate scatterplots to check for inconsistencies, unusual data needing further verification, and outliers. Regression diagnostics and exploratory analyses will be performed to find appropriate transformations of variables if needed. Order of priority in choosing a transformation will be to satisfy: 1) linearity, 2) homogeneity, and 3) normality assumptions. We will attempt to identify baseline covariates that predict attrition and compliance; and if identified, secondary analyses may need to incorporate stratification by these factors to decrease bias. As recommended by the National Academy of Sciences, [55] if the outcome is missing at random, we will attempt to identify baseline covariates that predict attrition and use these covariates to impute missing data based on multiple imputation. Sensitivity analyses, using pattern mixture models, will explore the effect of missing outcomes on inference if not at random.

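### The mixed models impose one baseline slope and one sex effect on both visits: negligible for total hip aBMD, a small and conditional cost for secondary outcomes and biomarkers, and almost free to fix

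*Protocol article*

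**What the plan says.** Section 2.8.3 names the independent variables of the primary model one by one: "visit (six and 12-months), treatment effect indicator (1 for risedronate; 0 for placebo"), the interaction of treatment with visit, then "participant sex (to account for randomization strata and sex as a relevant biologic variable), and baseline total hip aBMD value, assuming an unstructured covariance". The primary test is taken from this model, "using a contrast statement to test the 12-month treatment group difference using a 0.05 level of significance".

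The same list is then extended. Secondary models keep "all other covariates the same, except respective baseline values will be used in place of baseline total hip aBMD". For biomarkers, "Tertiary aim treatment effects will use the same models as the first two aims changing only the outcome and baseline covariate".

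The only other interactions named are sex or race/ethnicity with treatment, as sensitivity analyses; neither involves visit. On missing data, section 2.8.3 fits the models to completers, relies on baseline adjustment for robustness and promises sensitivity analyses for differential missingness. Section 2.8.1 adds "We will attempt to identify baseline covariates that predict attrition and compliance", with multiple imputation and pattern mixture models.

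**The concern.** This is an explicit list of terms, not a detail left open. The one interaction with visit is treatment, so the outcome's relation to its baseline, and the sex difference, must be the same at both visits.

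Under an unstructured covariance the shared slope is determined mainly by the less variable visit, usually six months, while the confirmatory contrast is at 12 months. Six months is the end of treatment; 12 months is half a year later. For an outcome whose link to baseline changes over that time, the slope applied at 12 months would be wrong. Two things could follow:

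- **Precision.** Baseline variation stays in the 12-month residual and widens the interval.
- **Bias.** If the analysed arms differ at baseline because dropout was selective in different ways by arm, the wrong slope under- or over-corrects the imbalance.

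**Working it through.** **1. The plan's own figure.** Section 2.8.2 gives a difference of 0.023 g/cm², SD 0.033, 48 evaluable per group, two-sided α 0.05. Noncentrality = (0.023/0.033) × √(48/2) = 3.41. Power is 92.2% (exact t, 94 df) or 92.7% (normal), so the stated 92% reproduces. It rests on a t-test and does not depend on the mixed-model terms.

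**2. Slopes for total hip aBMD.** If loss is proportional to baseline (assumption), the slope is 1 minus the fractional loss.
- Six months: 1 − 0.047/1.06 = 0.956 (pilot placebo loss in the Discussion; baseline in section 2.8.2).
- 12 months: 1 − 0.067 = 0.933 (section 2.8.2).

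**3. Error in the shared slope.** With residual SDs s6 and s12 and correlation r, the six-month visit has weight w6 = (s12² − r·s6·s12)/(s6² + s12² − 2r·s6·s12). The slope error at 12 months is w6 × (b6 − b12), and the excess 12-month variance is (slope error × baseline SD)²/s12².

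| | Total hip aBMD | Biomarker, r = 0.5 | Biomarker, r = 0.7 |
|---|---|---|---|
| Slopes, 6 and 12 months | 0.956, 0.933 | 0.7, 0.4 (assumed) | 0.7, 0.4 (assumed) |
| s6, s12 | 0.025 (assumed), 0.033 | 0.7, 0.9 (assumed) | 0.7, 0.9 (assumed) |
| r | 0.7 (assumed) | 0.5 (assumed) | 0.7 (assumed) |
| Baseline SD | 0.13 | 1 | 1 |
| w6 | 0.92 | 0.74 | 0.88 |
| Slope error × baseline SD | 0.0027 | 0.22 | 0.26 |
| Excess variance | 0.7% | 6.1% | 8.7% |
| Rise in SE | 0.3% | 3.0% | 4.2% |

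**4. Bias under selective dropout.** Among completers, bias = slope error × D, where D is the baseline difference between the retained arms. With 20% dropout, logistic in baseline and in opposite directions by arm, D is 0.118, 0.156 and 0.291 SD at log odds 0.3, 0.4 and 0.8 per SD. If the dropout pattern is the same in both arms, D = 0 and there is no bias.

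| Log odds per SD | Total hip aBMD (g/cm²) | Biomarker (SD) |
|---|---|---|
| 0.3 | 0.0003 | 0.03 |
| 0.4 | 0.0004 | 0.03–0.04 |
| 0.8 | 0.0008 | 0.06–0.08 |

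These are absolute sizes; the sign depends on which arm loses which patients.

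**5. Simulation** (120 patients, about 80% retained at 12 months in the dropout scenarios; listed model against the model with both visit-specific terms).
- *Total hip aBMD, slopes as in step 2.* With no dropout or the same dropout in both arms, the SE ratio (listed to visit-specific) was 0.998–1.008. With opposite dropout, bias was about 0.0008–0.001 g/cm² at log odds 0.8 and about 0.001 at log odds 1, roughly 4% of 0.023.
- *Biomarker, unequal slopes* (0.7/0.4, 0.4/0.7 or 0.3/0.7). Without baseline-related dropout the added terms cut the SE by 1.3–3.3% in one set of runs and by up to about 4% in others. At 0.7/0.4 and a 0.55 SD effect, power rose from 80.1% to 83.2%.
- *Biomarker 0.7/0.4, opposite dropout.* Bias was about -0.04 SD at log odds 0.3. At 0.8 it was -0.07 SD in completers only and -0.09 SD with dropouts' six-month data kept, that is 13–17% of 0.55 SD. With visit-specific terms it was about zero.
- *Biomarker 0.7/0.4, same dropout in both arms.* Bias was -0.001 SD, within simulation error of 0.003.
- *Sex effect differing by 0.02 g/cm² between visits* (assumed). The listed model's SE was 1–3% larger.
- *Equal slopes.* Power with and without the extra terms agreed within 0.1 point (88.6% and 88.5%; 89.5% and 89.4%).

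**The case against.** The strongest reply is that this is preference, not error. A common-slope mixed model is conventional and, absent arm-differential dropout, randomisation protects the contrast. The confirmatory outcome is practically untouched. The rest depends on assumed slopes, SDs and correlations, and the biomarker aims are exploratory and not formally powered. The bias needs three things at once: slopes that differ by visit, dropout driven by that outcome's own baseline, and a dependence that differs by arm in a double-blind trial. The plan already promises sensitivity analyses for missing data, and a fuller analysis plan might settle the terms.

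Most of this stands and sets the size of the point. It does not remove it: the article fixes the list without these terms for all three tiers, and none of the planned sensitivity analyses is said to add them.

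Two stronger readings are not supported. A reader might infer that the plan itself expects the harmful dropout. Sections 2.8.1 and 2.8.3 mention baseline predictors of attrition and differential missing data, but not baseline-related dropout that differs by arm. A reader might also try a much lower 12-month slope for total hip, such as 0.70, and find an SE 15–38% larger. That slope alone gives an SD of change of 0.30 × 0.13 = 0.039, above the 0.033 in Table 3; the stated figures require a slope of at least about 0.75. A gap of 0.10 (0.95 and 0.85) is compatible with Table 3 and would cost 3–6% in SE without arm-differential dropout, but nothing in the article points to it.

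**Conclusion.** The point holds as a minor improvement to the model specification. The primary analysis and its 92% power are sound as written. For secondary outcomes and biomarkers the likely cost is a slightly wider 12-month interval; bias is possible, but only under dropout that depends on that outcome's baseline differently in the two arms. The sizes for these outcomes are conditional: slopes, six-month SDs, correlations, dropout strength and the 0.55 SD effect are assumptions, because the article gives no baseline slopes for them. Whether any slope really changes between visits cannot be judged from the article.

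**What to change.** In section 2.8.3, add baseline-by-visit and sex-by-visit to the listed independent variables, state that they apply to the primary, secondary and tertiary models, and keep the 12-month and six-month treatment contrasts as they are. The cost is one line of text and two parameters per model, with no new data or patients. When the slopes are equal there is no measurable loss of power; the worst case seen was an SE about 1.5% larger, under strong arm-differential dropout. Make the change before unblinding, since adding the terms afterwards would be a data-driven model choice.

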### Primary outcome: DXA-derived total hip areal bone mineral density

2.4

This study is powered to detect significant group differences in change in total hip aBMD assessed by DXA over 12 months. The 12-month duration was selected to ensure adequate bone remodeling time in response to the intervention, [24] with inclusion of the six-month assessment to increase study power and allow for a midpoint safety assessment on all patients. DXA scans of the hip (as well as the lumbar spine, radius, and whole-body for secondary outcomes; see Section 2.4) will be acquired on an Hologic Horizon A device (Bedford, MA) and read by an International Society for Clinical Densitometry trained DXA technologist. Scans will be examined for proper patient positioning and exclusion of artifacts from the measured region; re-scanning will be performed as necessary. Daily quality control scans will be obtained with a calibration phantom, with repeat phantom scans if results are >2 standard deviations from baseline.

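### The primary mixed model is limited to undefined completers, which contradicts the intention-to-treat claim and drops the partial records that make the model robust

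*Protocol article*

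**What the plan says.** Section 2.8.3 specifies a linear mixed model for total hip aBMD with terms for "visit (six and 12-months), treatment effect indicator (1 for risedronate; 0 for placebo), the treatment by visit interaction", plus sex and "baseline total hip aBMD value, assuming an unstructured covariance". The primary test is the 12-month contrast, and the six-month effect comes from the same model. The section then sets the analysis set: "All models will use completers only, noting that mixed models with baseline covariate adjustments are fairly robust to missing data". It adds that unspecified sensitivity analyses will address differential missingness.

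Three other places bear on this:

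- Section 2.8.1: "Primary analyses will use intention-to-treat principles per CONSORT guidelines". If outcomes are missing at random, the authors will find baseline predictors of attrition and "use these covariates to impute missing data based on multiple imputation". It continues: "Sensitivity analyses, using pattern mixture models, will explore the effect of missing outcomes on inference if not at random".
- Section 2.4 justifies the intermediate visit: "with inclusion of the six-month assessment to increase study power and allow for a midpoint safety assessment on all patients".
- Section 2.8.2 plans for 80% retention at 12 months (48 of 60 per arm) and cites 87.5% retention at six months in the pilot.

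The article does not define completers. Its Discussion uses the word for the pilot in the ordinary sense, as the opposite of non-completers.

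**The concern.** An analysis that leaves out randomised patients because they did not finish is not intention-to-treat, so sections 2.8.1 and 2.8.3 cannot both describe the primary analysis.

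The reason given also undercuts the rule. A likelihood-based mixed model is robust under missing at random because a patient with a six-month value and no 12-month value stays in the likelihood and informs the 12-month mean through the covariance. A completers rule removes exactly those patients. What remains is essentially a 12-month ANCOVA, so the six-month visit no longer serves the power purpose stated in section 2.4. The six-month effect also loses patients who did have a six-month scan.

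The primary result is then not uniquely fixed. A completers model, an all-available-data mixed model (which the robustness clause implies) and multiple imputation (section 2.8.1) can give three different estimates of one endpoint.

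**Working it through.** **Inputs from section 2.8.2:** difference 0.023 g/cm², SD 0.033 g/cm², two-sided α 0.05, 60 randomised and 48 evaluable per arm, and pilot six-month retention of 87.5%, which is 0.875 × 60 = 52.5 per arm. **Assumed, because the article does not give them:** six/12-month correlation ρ of 0.5, 0.7 or 0.9, six-month SD of 0.025 g/cm² (needed in step 3 only), monotone dropout, and the dropout mechanisms.

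**1. The plan's own figure.** SE = 0.033 × √(2/48) = 0.00674, and 0.023/0.00674 = 3.41. The noncentral t-test with 94 df gives 92.2% power and the normal approximation 92.7%. The stated 92% reproduces. It is a t-test on 48 per arm and takes no credit for the six-month visit.

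**2. Who is affected.** At the pilot rate, 60 − 52.5 = 7.5 per arm (15 in total) leave before month six. A further 52.5 − 48 = 4.5 per arm (9 in total) leave after it. Together these are the 24 expected losses. The literal rule discards the six-month scans of the 9.

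**3. What the six-month rows add among completers.** Generalised least squares on the plan's model with 48 complete patients per arm gives these standard errors for the 12-month contrast:

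| ρ | 12-month ANCOVA | completers, both visits | plus 5 six-month-only patients per arm |
|---|---|---|---|
| 0.5 | 0.00681 | 0.00677 | 0.00669 |
| 0.7 | 0.00681 | 0.00678 | 0.00662 |
| 0.9 | 0.00680 | 0.00677 | 0.00651 |

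The six-month visit helps almost only through the patients whom the rule removes.

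**4. Power forgone.** With monotone dropout, the 12-month variance per arm with all available data is SD² × [(1 − ρ²)/n12 + ρ²/n6], so 1/n_eff = (1 − ρ²)/n12 + ρ²/n6. For ρ = 0.7: 0.51/48 + 0.49/52.5 = 0.01996, so n_eff = 50.1.

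| ρ | n_eff per arm | power | gain over 92.2% |
|---|---|---|---|
| 0.5 | 49.1 | 92.7% | 0.5 points |
| 0.7 | 50.1 | 93.2% | 1.0 points |
| 0.9 | 51.6 | 93.9% | 1.7 points |

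If all 60 per arm had a six-month scan (the upper bound), power would be 93.4%, 94.5% and 95.9%, a gain of 1.2 to 3.7 points.

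**5. Bias.** Suppose loss after month six depends on the six-month value in the placebo arm only, with larger bone loss making dropout more likely. The completers' placebo mean then shifts by ρ × 0.033 × m, where m is the amount, in SD units, by which the six-month mean of those who stay exceeds that of all patients seen at month six.

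- *Pilot pattern (12.5% lost before month six, 7.5% after), ρ = 0.7.* Of those seen at month six, 7.5/87.5 = 8.6% leave. If the odds of leaving double per SD of greater loss, m = 0.057, the shift is 0.7 × 0.033 × 0.057 = 0.0013, and completers give 0.0217. If the odds triple, m = 0.085, the shift is 0.0020, and completers give 0.0210. These shifts are 0.2 to 0.3 of the SE in step 1.
- *All 20% lost after month six, odds doubling, ρ = 0.5/0.7/0.9.* Completers give 0.0209/0.0200/0.0191. With opposite selection in the two arms they give 0.0186/0.0170/0.0154.
- *Same selection in both arms, or completely random loss.* Completers give about 0.023.

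In every scenario of the last two items, the model using all available data returned 0.023. Selection in the reverse direction would inflate the completers' estimate.

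**The case against.** The strongest defence is that completers is undefined and that the same sentence appeals to robustness against missing data, which would be pointless if everyone analysed had both visits. Together with the two-visit unstructured model and the intention-to-treat statement, the authors may have meant observed values without imputation. That is plausible as intent. The text does not say it, however, and an analyst who followed the words would discard data. Nor can the word mean pill adherence, because the per-protocol set is defined separately as at least five of six pills.

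Several stronger readings are tempting, and the documents do not support them:

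- *The trial has no protection against missing data.* Section 2.8.1 keeps multiple imputation and pattern-mixture models, and section 2.8.3 promises sensitivity analyses. The loss is confined to the primary model.
- *Completers are valid only as a random subset.* Dropout that depends on arm, sex or baseline aBMD does no harm, because all three are in the model.
- *The 92% power is overstated.* It never relied on the six-month visit.
- *A bias of 15 to 30% should be expected.* Figures of that size need most loss to fall after month six, against the pilot pattern, or opposite selection in the two arms of a double-blind trial.

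An all-available-data model is not a complete cure either. If dropout follows six-month weight change, and weight change predicts 12-month aBMD beyond six-month aBMD, that model is biased too, because weight is not in it. It also leaves out the roughly 15 patients expected to have no post-baseline scan.

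**Conclusion.** Wrong as written. The completers rule in section 2.8.3 contradicts the intention-to-treat statement in section 2.8.1, removes the records on which its own justification depends, and defeats the power purpose given for the six-month visit in section 2.4. None of this depends on a simulation.

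The numerical consequence is modest under the pilot's retention pattern: about 0.5 to 1.7 power points forgone, and about 0.021 against 0.023 g/cm² under assumed placebo-only selection with ρ = 0.7. It is larger under stronger or opposite selection and nil if selection is equal in the two arms. The correlation and the dropout mechanisms are assumptions. The article gives no evidence that dropout will differ by arm, so the bias is a risk and not a forecast.

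**What to change.** Replace the completers sentence in section 2.8.3 with:

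> The primary model includes all randomised participants with at least one post-baseline total hip aBMD value, analysed as randomised, using all available six- and 12-month data by REML; a completers analysis is a labelled sensitivity analysis.

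In section 2.8.1, state that the multiple imputation, which also covers patients with no post-baseline value, and the pattern-mixture models are sensitivity analyses. One primary analysis is then fixed before unblinding. Apply the same analysis-set rule to the secondary and tertiary models, since the sentence governs all of them.

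The cost is a few sentences of analysis wording. It needs no extra patients, visits or data.

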## Discussion

3

The STRONG BONES trial is designed to definitively test whether musculoskeletal tissue loss following SG surgery can be mitigated through transient bisphosphonate therapy. Increasing utilization of SG to treat severe obesity, alongside increasing awareness of the skeletal complications of bariatric surgery, underscores the timeliness of this research question. If confirmed, data from this trial will present risedronate as a potential surgical adjuvant, aimed at maximizing the cardiometabolic benefits of SG surgery, while minimizing potential harm to the musculoskeletal system.

Bisphosphonates are a class of drugs that have been used commonly for more than two decades for the treatment and prevention of osteoporosis. As a class, these medications are particularly well absorbed in the trabecular region of the femoral neck and spine, [12] and have a potent effect on bone remodeling by inhibiting the breakdown of hydroxyapatite (the primary structural component of bone). [59] We specifically selected risedronate due to its efficacy, safety, [60,61] once-monthly dosing regimen, and low cost. [62] Together, the few reported AEs (5 total; 3.7% AE rate), high degree of protocol adherence (100% adherence among completers; 92% when non-completers were included), [15] and signal for total hip aBMD sparing [risedronate: -0.028 g/cm^2^ (−0.049, −0.006) vs. placebo: -0.047 g/cm^2^ (−0.063, −0.030)] at six months in the pilot study [15,16] provided impetus for the STRONG BONES trial primary aim and hypothesis.

That said, bariatric surgery patients are at heightened risk of developing hypocalcemia, [63] which may be elevated with concomitant bisphosphonate use. [64] Fortunately, hypocalcemia was not observed during the pilot study, however we still have planned safety measures to mitigate risk of this serious complication. All participants are screened at baseline to ensure serum calcium is within the normal range (8.6–10.2 mg/dL) and vitamin D levels are non-deficient (>20 ng/mL). Once enrolled, and in addition to nutrition counseling from their surgical team, all study participants receive a 6-month supply of the Celebrate Essential Multi 2-in-1 multivitamin, which provides ∼30% and ∼95% of the RDI for calcium and vitamin D, respectively (see *Section 2.2.1*). Additionally, routine post-operative clinical visits are scheduled at 1- and 3-months post procedure, where serologic markers are assessed; and, a fasting blood draw will be collected at the 6- and 12-month study visit to assess safety-related labs (including: calcium, vitamin D, eGFR, and parathyroid hormone). Finally, as a NIAMS-funded clinical trial, this study is overseen by an external, 5-member data safety monitoring board, which meets biannually to help the study team ensure participant safety and data integrity are prioritized throughout the trial.

This trial is also designed to offer additional insight into the biology of SG-associated lean mass loss, as well as potential counteractant effects of risedronate use. We specifically build off the appendicular lean mass sparing signal observed in the pilot study [risedronate: -1.2 kg (−2.3, −0.1) vs placebo: -2.1 kg (−3.0, −1.2)] to explore whether the blunting of SG-associated bone resorption can preserve muscle via bone-muscle crosstalk. As the field of bone-muscle crosstalk is rapidly evolving, our robust specimen storage will serve as a valuable resource for future work in this area. Ultimately, these data may also inform lean-mass research endeavors in related fields, such as exercise enhancement, sarcopenia prevention, and spaceflight safety.

Clinical recommendations to optimize bone outcomes following bariatric surgery include adequate consumption of calcium (1200–1500 mg/day), vitamin D (2000–3000 IU/day), and protein (60–75 g/day), along with regular weight-bearing exercise. [7,22] Increasingly, studies are being designed and implemented to test osteoprotective strategies, with many active trials registered on clinicaltrials.gov. Pertinent among these, are two exploring lifestyle-based therapies (NCT04193397, NCT04777305) studying either resistance training alone, or comparison of resistance training, aerobic training, or a combination of the two, and three (not including the STRONG BONES trial) are exploring pharmacotherapies (NCT04279392, NCT04087096, NCT04742010), using zoledronic acid or comparing zoledronic acid with denosumab. Two trials have been completed looking at mega-dosing vitamin D (NCT02092376) and the effects of tele-counseling behavioral counseling and a 12-week supervised exercise program (NCT03214471). As skeletal effects of bariatric surgery are multifactorial, future work in this area will likely aim to couple therapeutic strategies.

